### Endpoint

The primary endpoint of the study is to evaluate the technical and clinical success of EVAR with Alto stent graft in short- (90-day), mid- (1-year), and long-term (5-year) follow-up periods. Technical success is defined as the correct graft deployment without any unintentional occlusion of the aortic visceral branches or both hypogastric arteries, with aneurysm exclusion confirmed by the intraoperative angiography, without signs of type I/III endoleak or conversion to open surgery or mortality. Clinical success includes successful deployment of the endovascular device at the intended location without death as a result of aneurysm-related treatment, type I or III endoleak, or graft infection or thrombosis, aneurysm expansion (>5 mm), aneurysm rupture, or conversion to open repair. Moreover, the presence of graft dilatation of 20% or more by diameter, graft migration, or a failure of device integrity will be evaluated.

The clinical and technical successes are defined “assisted” in case of unplanned endovascular procedures, or “secondary” if unplanned surgery is necessary [19].

The following secondary endpoints will be also addressed: (1) operative time; (2) intraoperative radiation exposure; (3) contrast medium usage; (4) AAA sac shrinkage at 12-month and 5-year follow-up; (5) any potential role of patients’ baseline characteristics, valuated on preoperative CTA, and of device configuration (number of component) in primary endpoint.

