**Methods:**

All consecutive eligible patients submitted to endovascular aneurysm repair (EVAR) by Alto Endovascular AAA implantation will be included in this analysis. Patients will be submitted to EVAR procedures based on their own preferences, anatomical features, and operators experience. An estimated number of 300 patients submitted to EVAR with Alto stent graft should be enrolled. It is estimated that the inclusion period will be 24 months. The follow-up period is set to be 5 years. Full data sets and cross-sectional images of contrast-enhanced computed tomography scan performed before EVAR, at the first postoperative month, at 24 or 36 months, and at 5-year follow-up interval will be reported in the central database for a centralized core laboratory review of morphological changes. The primary endpoint of the study is to evaluate the technical and clinical success of EVAR with the Alto stent graft in short- (90-day), mid- (1-year), and long-term (5-year) follow-up periods. The following secondary endpoints will be also addressed: operative time; intraoperative radiation exposure; contrast medium usage; AAA sac shrinkage at 12-month and 5-year follow-up; any potential role of patients’ baseline characteristics, valuated on preoperative computed tomography angiographic study, and of device configuration (number of component) in the primary endpoint.

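### Technical success is a primary endpoint at 90 days, 1 year and 5 years but is defined at the procedure, with conversion and mortality left undated

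*Protocol article*

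**What the plan says.** The Endpoint section of the protocol article names as primary the "technical and clinical success of EVAR with Alto stent graft in short- (90-day), mid- (1-year), and long-term (5-year) follow-up periods". The Methods part of the Abstract repeats this: the aim is to "evaluate the technical and clinical success of EVAR with the Alto stent graft in short- (90-day), mid- (1-year), and long-term (5-year) follow-up periods". In both places the three times attach to technical and clinical success together.

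The Endpoint section then gives the definitions.

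- **Technical success, deployment:** "Technical success is defined as the correct graft deployment without any unintentional occlusion of the aortic visceral branches or both hypogastric arteries".
- **Technical success, remainder:** "with aneurysm exclusion confirmed by the intraoperative angiography, without signs of type I/III endoleak or conversion to open surgery or mortality". Neither conversion nor mortality has a time limit, and mortality has no cause restriction.
- **Clinical success, deaths:** "without death as a result of aneurysm-related treatment, type I or III endoleak, or graft infection or thrombosis". Only deaths due to aneurysm-related treatment count. This definition also holds the components that need follow-up, such as sac expansion and rupture.
- **Labels:** both kinds of success are called assisted "in case of unplanned endovascular procedures", and secondary when unplanned surgery is needed. No window is given for either label.

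Two other places bear on this. The paragraph after the exclusion criteria counts a patient as enrolled only if the criteria are met and the repair was successful on the completion angiogram. The Data Collection and Analysis section plans Kaplan-Meier life tables from the procedure date for time-dependent events.

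**The concern.** A measure read on an angiogram in the operating room cannot change at 90 days, 1 year or 5 years. A primary endpoint that asks for it at those times must either repeat one number or be turned into something else, and the article does not say which. The only components that could change without re-imaging are conversion and mortality, and these are the ones without a window.

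At stake is the interpretation of part of the primary endpoint. A figure published as 5-year technical success could be taken for durability when it is either a day-of-surgery result or a quantity driven largely by deaths from other causes. Secondary endpoint 5 relates baseline characteristics and number of components to the primary endpoint, so on the time-updated reading those comparisons would partly reflect background mortality.

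**Working it through.** The article gives 300 patients as an estimate without a target rate or precision, so there is no figure of its own to reproduce. The check sorts the components of technical success and then illustrates the two readings.

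**Step 1. When each component is settled**

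| Component of technical success | When settled |
|---|---|
| Correct deployment, no unintentional branch occlusion | At the procedure |
| Exclusion without type I/III endoleak | At the procedure, on the intraoperative angiogram |
| No conversion to open surgery | Undated |
| No mortality | Undated, any cause |

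**Step 2. Reading A: everything fixed at the procedure.** The value is the same at all three times. Enrolment after a successful completion angiogram selects on most of the components, so the observed proportion would be close to 300/300. The exact (Clopper-Pearson) lower limit for 300/300 is 0.025^(1/300) = 0.988, giving a 95% CI of 98.8% to 100%. If failures could be observed, 300 patients would give an informative estimate: 294/300 has an exact 95% CI of 95.7% to 99.3%, and 285/300 one of 91.9% to 97.2%.

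**Step 3. Reading B: undated components carried forward.** Let m, c and e be annual rates of all-cause death, open conversion and later type I/III endoleak. All are assumed; none is in the article. Starting from 100%, success at t years is ((1 − m)(1 − c)(1 − e))^t.

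| Assumed m per year | 90 days, death only | 5 years, death only | 5 years, with c = 0.5% |
|---|---|---|---|
| 2% | 99.5% | 90.4% | 88.2% |
| 3% | 99.3% | 85.9% | 83.7% |
| 5% | 98.7% | 77.4% | 75.5% |
| 8% | 98.0% | 65.9% | 64.3% |

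For example, 0.98^5 = 0.904, which is 100 − 90.4 = 9.6 points below reading A.

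**Step 4. What drives reading B.** The share of failures that are deaths is ln(1 − m) / [ln(1 − m) + ln(1 − c) + ln(1 − e)]. With c = 0.5% and e = 0 it runs from 80% (m = 2%) to 94% (m = 8%). Adding e = 1% lowers it to between 57% and 85%. Deaths predominate in these scenarios, but the quantity is not all-cause survival.

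**Step 5. Comparison with clinical success.** Under reading B, a death unrelated to the aneurysm or its treatment is a technical failure but not a clinical one, so the procedural measure is the stricter of the two on death.

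**The case against.** The strongest reply is that the definition itself settles the matter. Conversion and mortality stand in a sentence tied to the intraoperative angiogram, the components that need follow-up are under clinical success, and the stated objective separates intraoperative, perioperative and postoperative results. The natural reading is then technical success at the procedure and clinical success at the three times. This is probably what is meant, but the article does not say so. Both statements of the primary endpoint attach all three times to both outcomes, and the undated assisted and secondary labels apply to technical success too.

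A second reply is that a condensed article may leave the exact window to the full protocol or analysis plan. That would answer a mere omission. Here the stated times and the stated definition do not fit each other, and an analysis plan cannot follow both as written.

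Other parts of the case against stand. Reading A is redundant, not biased: procedural success keeps its meaning and clinical success still carries durability. Nothing in the article says that deaths up to 5 years will count as technical failures. The larger gaps in the table rest on assumed mortality, and the upper rates are hard to square with the exclusion of patients whose life expectancy is shorter than follow-up.

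**Conclusion.** The point holds as a conflict within the stated primary endpoint: three follow-up times are attached to a measure defined at the procedure, and two of its components are undated. This does not depend on any assumed rate.

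The size does. On the literal reading the cost is one procedural proportion given three times, drawn towards 100% by the enrolment rule. On the time-updated reading, the shortfall at 5 years is about 10 points with an assumed 2% mortality a year, and larger if mortality is higher.

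A reader might infer that half of the primary endpoint is meaningless, or that the 5-year figure will be all-cause survival. The documents support neither. Technical success is meaningful as a procedural measure, and the time-updated version would be survival free of open conversion, and of type I/III endoleak only if that were re-read at follow-up. The correction is worth making because it concerns the primary endpoint and its core is a change of wording.

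**What to change.** 1. In the Endpoint section and the Methods part of the Abstract, state that technical success is assessed once, at the index procedure, with conversion and mortality limited to one stated procedural window. Tie the assisted and secondary labels for technical success to the same window.
2. Assign 90 days, 1 year and 5 years to clinical success alone.
3. Report technical success among all consenting eligible patients in whom Alto implantation was attempted, and amend the enrolment sentence after the exclusion criteria to match.

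Items 1 and 2 change only the wording and the layout of the results tables. Item 3 costs more: basic procedural data must be recorded for failed attempts, which the present rule leaves out of the registry, and the reported success rate may be slightly lower.

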### Data Collection and Analysis

Patient data will be captured electronically using a computer-based platform accessible to all investigators. Descriptive data summaries will be used to present and summarize the collected data. For categorical variables (eg, gender), frequency distributions and cross tabulations will be given. For numeric variables (eg, patient age), range, mean, median, and SD will be calculated. For all variables, a 95% CI for the relevant parameters of the underlying distribution will be calculated. For all time-dependent events, life tables will be calculated using the Kaplan-Meier estimate method for a period starting on the date of the procedure up to and including all follow-up visits. Stratification to risk factors will be performed and the log-rank test will be used to compare between the different outcomes; associated *P* values <.05 will be defined as significant.

All preoperative and follow-up CTAs were assessed and independently evaluated by 2 experienced vascular surgeons at core laboratory center. Disagreements will be discussed and resolved by consensus.

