## Introduction

### Background

An abdominal aortic aneurysm (AAA) is a dilatation in the lower part of the major vessel (aorta) that supplies blood to the body. The most accepted definition of AAA is based on a diameter of 3.0 cm or more, which is usually higher than 2 SDs above the mean diameter for men [1,2]. Over the last decades, the treatment options have changed. The traditional approach is represented by the open surgical repair [3,4]. As an alternative, the less invasive endovascular treatment has been proposed (endovascular aneurysm repair [EVAR]), which has become the first treatment of choice in patients with suitable anatomy [5,6]. EVAR represents a minimally invasive technique that has overcome some critical issues of open surgical repair such as higher intraoperative and perioperative risk; the necessity of general anesthesia; intensive care unit stay; and higher cardiac, pulmonary, and renal complications [7]. These advantages led to a constant increase in the AAA treatment feasibility, especially in elderly patients with a substantial number of comorbidities that could be treated with reasonable perioperative risks [8] and good early and mid-term outcomes [9] even in emergency settings [10].

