**Exclusion Criteria**
Abdominal endovascular aneurysm repair performed in an urgent/emergent setting.Patients treated outside Endologix Alto endograft device’s instruction for use.Patients refusing treatment.Patients for whom antiplatelet therapy, anticoagulants, or antihypertensive drug are contraindicated.Patients with a history of prior life-threatening contrast medium reaction.Life expectancy less than the follow-up period.

A patient is considered enrolled in the study if he/she has full compliance with the study inclusion and exclusion criteria and after successful EVAR procedure at completion angiography.

Clinical data will be collected at patients’ enrollment, EVAR procedure, discharge, planned follow-ups (1-3 and 12 months after the procedure, yearly thereafter), unplanned or interim follow-ups, and patient death. CTA within 90 days, 24 or 36 months, and 5 years after the index procedure is mandatory. Duplex ultrasound scan will be performed at the same follow-up interval, and also at 12, 24, 36, and 48 months. A new CTA will be performed in case of unexpected events during follow-up. The follow-up protocol is based on the most recent European guidelines for the management of the AAAs [1].

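### Kaplan-Meier for every time-dependent event censors deaths not counted as clinical failure, so 1-KM overstates the 5-year proportion of patients who fail, probably modestly

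*Protocol article*

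**What the plan says.** Data Collection and Analysis names one estimator for all time-to-event outcomes: "For all time-dependent events, life tables will be calculated using the Kaplan-Meier estimate method". The clock runs from the day of implantation through the last visit. Risk-factor strata are compared by log-rank test at the 5% level.

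Endpoint makes clinical success part of the primary endpoint over "short- (90-day), mid- (1-year), and long-term (5-year) follow-up periods". Success requires that the device is deployed where intended. The list of failures that must be absent begins "without death as a result of aneurysm-related treatment, type I or III endoleak, or graft infection or thrombosis"; it also names expansion of more than 5 mm, rupture and conversion to open repair. The only death that counts as failure in its own right is one caused by the treatment. A fatal rupture counts through the rupture component.

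Two further statements matter. The data-collection paragraph that follows the exclusion criteria lists "unplanned or interim follow-ups, and patient death" among the points at which clinical data are recorded, so deaths will be observed. The exclusion list contains "Life expectancy less than the follow-up period", with follow-up set at 5 years. The article does not mention competing risks or cumulative incidence, and does not say how a death that is not a failure enters the analysis.

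**The concern.** Kaplan-Meier has two states for a patient at a given time: event, or still able to have the event unless censored. A patient who dies of, say, cancer in year 3 without clinical failure is not an event under the Endpoint definition, so the method censors that patient. Censoring spreads the patient's remaining probability over those still followed, as though the dead patient could yet have an endoleak, expansion or conversion. The resulting 1-KM is the failure risk in a hypothetical population in which nobody dies of other causes. The article does not declare that as its target.

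At stake is the 5-year estimate of clinical failure and of each non-fatal component. A reader will naturally take such a curve as the share of treated patients who fail, and on that reading it is too high. The long-term horizon is also the one on which the Discussion rests its hope of confirming durability.

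**Working it through.** **Inputs.** The article states no failure rate, mortality rate or sample-size derivation, so there is no figure of its own to reproduce. From the documents: 300 patients, horizons of 90 days, 1 year and 5 years, the Kaplan-Meier prescription and the definition of failure. Assumed: constant, independent cause-specific hazards; a 5-year 1-KM failure F of 5%, 15% or 30%; and a 5-year risk M of death not counted as failure (taken net of failure) of 10%, 20% or 30%.

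**Direction.** This needs none of the assumed rates. At each failure time the Kaplan-Meier curve and the Aalen-Johansen estimate use the same ratio of failures to patients at risk. Kaplan-Meier multiplies it by the probability of being failure-free, ignoring other deaths. Aalen-Johansen multiplies it by the probability of being both failure-free and alive. The first multiplier is never smaller, and it is larger once a non-counted death has occurred. So 1-KM is the higher estimate whenever such deaths happen while failures are still accruing.

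**Size at 5 years.** With h1 = -ln(1-F)/5 and h2 = -ln(1-M)/5:

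- 1-KM at time t tends to 1 - exp(-h1·t)
- actual cumulative incidence = h1/(h1+h2) × [1 - exp(-(h1+h2)·t)]

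For F = 15% and M = 20%: 5·h1 = 0.1625 and 5·h2 = 0.2231. The ratio is 0.1625/0.3857 = 0.4214, and the bracket is 1 - 0.85 × 0.80 = 0.32. The product is 0.1348, so the excess is 15.0 - 13.5 = 1.5 points.

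| 5-year 1-KM | M = 10% | M = 20% | M = 30% |
|---|---|---|---|
| 5% | 4.75% (excess 0.25) | 4.5% (0.5) | 4.2% (0.8) |
| 15% | 14.3% (0.7) | 13.5% (1.5) | 12.7% (2.3) |
| 30% | 28.6% (1.4) | 27.1% (2.9) | 25.5% (4.5) |

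Cells give the actual cumulative incidence, with the excess of 1-KM in percentage points in brackets. In relative terms the overstatement is about 5%, 11% and 18% for the three values of M. In the 15% row the excess corresponds to about 2, 5 and 7 of 300 patients.

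**Earlier horizons.** Keeping the hazards for F = 15% and M = 30%:

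- 90 days (t = 0.25): 0.81% against 0.80%, an excess of about 0.01 points
- 1 year: 3.20% against 3.09%, an excess of 0.11 points
- 5 years: 15.0% against 12.7%, an excess of 2.3 points

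**Scale.** Ignoring censoring, the 95% confidence half-width for 15% with 300 patients is 1.96 × √(0.15 × 0.85/300) = 0.040, or about 4.0 points.

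**The case against.** The strongest defence is that the effect is small, confined to one horizon and harmless to any stated decision. Two of the three primary horizons are essentially untouched. At 5 years the excess in the 15% scenarios lies inside the sampling error of 300 patients. The registry is single-arm and descriptive, with no performance goal, and the bias makes the device look worse. All of this stands and limits the weight of the point. It does not remove the point, because the bias does not shrink as patients are added and is cheap to avoid.

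A second defence is that freedom from failure among patients still alive is a recognised durability target. That is fair, but the article does not say it wants this target, and the same curves will be read as the proportion failing. It is a reason to keep the curve as a supporting figure.

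A third is that Data Collection and Analysis also prescribes frequency distributions with confidence intervals, so the headline result might not be 1-KM. That is possible, since the article does not say which summary carries the primary endpoint. Its sentence on time-dependent events is nonetheless universal, so any time-to-event curve of failure falls under it.

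Two stronger readings may tempt a reader. The first is that the log-rank comparisons are distorted by differing mortality between strata. They are not, under the independence assumed here: a log-rank test that censors other deaths compares cause-specific failure hazards. Two strata with the same 15% 1-KM and 10% against 30% other-cause death have identical Kaplan-Meier curves but cumulative incidences of 14.3% and 12.7%. It is cumulative incidence, not the log-rank test, that responds to mortality. Nor does the article say that log-rank results will be read as absolute risk.

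The second is that competing mortality in this registry must be high because Background says treatment has grown "especially in elderly patients with a substantial number of comorbidities". That sentence concerns EVAR in general. The registry excludes patients not expected to live through follow-up, and Recruitment asks for a stable condition and no illness that would prevent completion. Both point towards the lower mortality scenarios. Neither can make other-cause death zero over 5 years, since each is a judgement made at entry.

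**Conclusion.** The point holds as a modest one. The prescribed estimator does not match a failure definition that leaves out deaths unrelated to the aneurysm or its treatment, and nothing in the article repairs this. The direction is certain once such deaths occur while failures are still accruing. The size cannot be determined from the documents. Under constant hazards and a 5-year 1-KM of 15%, the excess is about 0.7 to 2.3 points for 10% to 30% other-cause death, with the lower end more plausible given the entry criteria. At 10% other-cause death it is at most 1.4 points in the scenarios examined. Results at 90 days and 1 year are practically unaffected, the error is conservative for the device, and the log-rank test remains valid for cause-specific hazards. This is an inexpensive improvement to the 5-year report and no threat to the registry's validity.

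**What to change.** Restrict the Kaplan-Meier sentence to overall survival and add wording along these lines: for time-to-event endpoints other than all-cause death, cumulative incidence will be estimated by the Aalen-Johansen method with 95% confidence intervals, at least at 5 years, treating death not counted as failure as a competing event. Show overall survival beside the failure curves, and keep cause-specific Kaplan-Meier freedom-from-failure curves as a supporting figure for comparison with older series.

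The log-rank test may stay for the risk-factor comparisons, with a statement that it compares cause-specific hazards and not absolute 5-year risk. If a comparison of absolute risk is wanted, Gray's test on cumulative incidence is the matching choice.

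The cost is a few sentences and standard software. No visit, scan or design feature changes. Death is already recorded, and the Endpoint definition already requires deciding whether a death resulted from aneurysm-related treatment. The change should be made before the 5-year data are analysed.

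### One visit-based Kaplan-Meier window covers events that only imaging can show, so 5-year clinical success is overstated if patients miss scans but keep attending

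*Protocol article*

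**What the plan says.** Data Collection and Analysis gives one rule for all outcomes: "For all time-dependent events, life tables will be calculated using the Kaplan-Meier estimate method", and the window runs "for a period starting on the date of the procedure up to and including all follow-up visits". It does not separate events by how they are detected.

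The Endpoint section defines clinical success as successful deployment without aneurysm-related death, "type I or III endoleak, or graft infection or thrombosis, aneurysm expansion (>5 mm), aneurysm rupture, or conversion to open repair". It is assessed "in short- (90-day), mid- (1-year), and long-term (5-year) follow-up periods".

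The follow-up paragraph after the Exclusion Criteria lists the data-collection points, including "planned follow-ups (1-3 and 12 months after the procedure, yearly thereafter), unplanned or interim follow-ups, and patient death". It then sets the imaging. On CTA the rule is: "CTA within 90 days, 24 or 36 months, and 5 years after the index procedure is mandatory". Ultrasound is planned more often than CTA, on these terms: "Duplex ultrasound scan will be performed at the same follow-up interval, and also at 12, 24, 36, and 48 months". Outside the fixed schedule there is one further provision: "A new CTA will be performed in case of unexpected events during follow-up".

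**The concern.** Rupture, conversion and death come to light whether or not a scan is done. Type I/III endoleak and sac expansion do not. For these, a visit without imaging says nothing about whether the patient has failed.

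If time at risk is carried to the last visit for all events, a patient last scanned at 1 year who attends until year 5 adds four event-free years for failures that nobody could have found. The patient stays in the denominator and cannot enter the numerator. The error favours the device, it grows as imaging compliance falls, and it affects the 5-year primary result. It is also separate from how a detected failure is dated: it would remain if every detected failure had its exact date.

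**Working it through.** The article gives no event rate, expected success rate or missed-imaging rate, so there is no figure of the plan to reproduce. The check has a documentary part and an illustrative part.

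**1. Does the schedule leave planned visits without a scan?**

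| Planned visit | Planned imaging |
|---|---|
| 1-3 months | CTA within 90 days, with duplex |
| 12 months | duplex |
| 24 and 36 months | duplex at both, CTA at one |
| 48 months | duplex |
| 5 years | CTA, with duplex |

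No. As planned, the last planned visit is also the last scan. A gap opens only if a scheduled scan is missed and the patient is still seen afterwards. An interim visit between two completed scans does no harm: when failures are dated at scans, it changes no risk set.

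**2. Size if scans are missed.** All of these inputs are assumptions:
- imaging-detected failure at a constant rate h of 2%, 3% or 4% per year;
- imaging drop-out at a rate g of 5% or 10% per year, so that 1 − e^(−5g) = 22% or 39% have stopped by year 5;
- patients who stop imaging still attend until death or year 5;
- death and imaging drop-out independent of failure;
- scans at 2, 12, 24, 36, 48 and 60 months, with failures dated at the scan.

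True 5-year freedom from failure is e^(−5h). With analysis to the last visit, the share detected at scan k is d_k = e^(−g·t_k) × [e^(−h·t_(k−1)) − e^(−h·t_k)], and the 5-year estimate is 1 − Σd_k. Independent death cancels out.

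For h = 3% and g = 5%: Σd_k = 0.0049 + 0.0234 + 0.0260 + 0.0240 + 0.0221 + 0.0204 = 0.1208. The estimate is 87.9% against a true 86.1%.

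| h per year | True | To last visit, 22% stopped | To last visit, 39% stopped |
|---|---|---|---|
| 2% | 90.5% | 91.8% (+1.3) | 92.8% (+2.3) |
| 3% | 86.1% | 87.9% (+1.9) | 89.5% (+3.4) |
| 4% | 81.9% | 84.3% (+2.4) | 86.3% (+4.4) |

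Differences are taken before rounding. With g = 0 the overstatement is zero. Under these assumptions, ending time at the last scan recovers the true value.

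**3. Cross-check with a simpler model.** If a share m stops scanning after year 1 and nobody dies, the overstatement is m × (S1 − S5). With S5 = 0.90, S1 = 0.90^(1/5) = 0.979. For m = 20% this is 0.20 × (0.979 − 0.900) = 1.6 points. For true freedom of 0.80 to 0.95 and m of 10% to 40%, simulations with the stop after year 1 or at a random visit gave 0.3 to 6.3 points, always upward.

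**4. Yardstick.** The simple binomial 95% half-width at 86.1% and n = 300 is 1.96 × √(0.861 × 0.139 / 300) = 3.9 points. Censoring would widen it.

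**5. Does the remedy bring a bias of its own?** It does if event-free patients leave at the last scan while clinical events after that scan still count. Add an assumed 1% per year of clinically evident failure to h = 3%, with 39% stopped. True composite success is e^(−0.20) = 81.9%. In simulation, analysis to the last visit gives 85.1% and the asymmetric rule gives 80.3%. A rule that closes follow-up at the same point for events and non-events, when the next scheduled scan falls due and is not done, gives 81.9%. Over a range of assumed rates the asymmetric rule over-counts failure by about 0.2 to 1.7 points.

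**The case against.** The strongest reply is that the defect is not in the text. The sentence describes an observation window, never uses the word censor, and does not say that unscanned patients count as event-free. Censoring dates by component are normal content of a SAP or full protocol, neither of which is shown. A reader might infer that the plan prescribes censoring at the last visit. The article does not say so, and that part of the reply stands. What remains is that the article does more than stay silent: it states one visit-based window and applies it to all time-dependent events. Last-visit follow-up is the natural reading, and a SAP that follows the sentence would carry the problem forward.

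The second reply is that imaging is planned at every planned visit and that patients must be willing to comply with follow-up. This also stands, and it makes the point conditional. A reader might infer that 5-year success will be overstated as planned. The documents support only that it would be if scheduled scans are missed. A schedule does not guarantee five years of adherence in a registry, and the extra CTA is tied to unexpected events, so it does not cover a scan that was simply skipped.

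Third, the drop-out rates come from no document, and the assumption that everyone who stops imaging keeps attending is a worst case. This stands too.

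Finally, a reader might infer that the centres that scan least would look best. No comparison of centres is planned, so the documents give no basis for it.

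**Conclusion.** The point holds in conditional form. The stated window does not fit the imaging-dependent part of the primary composite. If patients miss scheduled scans but are still seen, analysis to the last visit biases 5-year clinical success upward; if imaging is complete there is no bias.

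Under the assumed rates the overstatement is about 1 to 4 points, or roughly one third of the half-width to slightly more than all of it (1.3/3.9 to 4.4/3.9). That comparison is only a sense of scale: the half-width is worked out at 86.1% success, while the two ends of the range belong to other success rates. The direction follows from the logic, but the size rests wholly on assumption. It merits a change of wording before the 5-year data are seen; it does not show that the registry's results will be wrong.

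**What to change.** In Data Collection and Analysis:

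- State that for type I/III endoleak, expansion and the other imaging-dependent components, and for composite clinical success, follow-up ends at the last adequate scan (duplex or CTA), for events and non-events alike. Define an adequate scan.
- Say how clinical events between scans are handled. A rupture normally follows that patient's last scan, so a literal cut at the scan date would drop it. One workable wording is that the interval opened by a scan stays open until the next scheduled scan falls due. Clinical events inside that interval count; after a missed scan, neither events nor event-free time count.
- Analyse rupture, conversion, infection and aneurysm-related death separately, to last contact, so that no late clinical event is lost from the report.
- Add a sensitivity analysis that counts late clinical events in the composite.
- Show the number imaged at each time point under the curves, beside the number followed.

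No new data collection should be needed beyond the dates of scans that the protocol already schedules. The price is fewer patients at risk at 5 years and a wider interval. With assumed 5% yearly mortality and 10% yearly imaging drop-out, and ignoring failures, 300 × e^(−0.25) ≈ 234 would be alive at 5 years and 300 × e^(−0.25) × e^(−0.5) ≈ 142 still imaged. The method also assumes that patients who stop imaging have the same later risk as those who continue, which is why imaging completeness should be reported.
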